#### Missing covariate data

Imputation of missing covariate data will be carried out using multiple imputations through chained equations (MICE) [45, 46]. However, this will only be relevant for models including covariates.

#### Non-adherence

For the augmented standard of care arm, an indicator of non-adherence will be defined if the following 2 criteria are met: < 6 regular contacts and an intake of < 80% of the calculated protein and energy requirement for at least one third of the intervention period. It will not be possible to make comparisons between the two intervention arms. However, changes within the augmented standard of care arm will be estimated using a logistic mixed-effects model including time as a fixed effect and blocks and participants as random effects. The estimated changes in non-adherence from baseline to 1 and 3 months will be reported as odds ratios together with the corresponding 95% confidence intervals and *p* values.

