#### Nutritionally augmented standard of care

The intervention has been designed by a multidisciplinary team of experts within pulmonary medicine, infections, nutrition, and physical (in)activity. The intervention has a duration of 12 weeks. In addition to standard of care, the intervention contains four elements including (1) individual nutritional plan, (2) regular contact, (3) adherence support, and (4) weight diary. The four elements are described below:*Nutritional plan* is developed and adjusted with the participant based on nutritional registration, information about routines and habits and nutritional preferences to reach a daily protein target of 1.5 g protein/kg/day [17] and individual energy requirements of 30–45 kcal/kg/day [17]. The nutritional plan is adjusted at the regular contacts. The nutritional plan may include supplementation with energy and protein-rich products and during the intervention period, a document summarizing tools and advices are provided.*Regular contacts* are phone calls from the project coordinator every 7–14th day to talk about the nutritional plan, well-being, adherence, or potential side effects.*Adherence support* is provided through the regular contact and a friendly reminder that encourages the participant to follow the nutritional plan and to ask for support (a note to hang on the refrigerator).*Weight diary* is a daily registration of weight.

Note: It is likely that participants in both groups will be hospitalized during the intervention period. As far as possible the study coordinator will continue the intervention during hospitalization. Hospitalizations with acute infections such as pneumonia and exacerbation are common among individuals with severe COPD and both conditions increase nutritional requirements. It is therefore essential to maintain the contact with nutritional and mental support during hospitalization.

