### Data collection for participants who discontinue or deviate from intervention protocols

Deviation from the intervention is defined as less than 6 regular contacts and an intake of less than 80% of the calculated protein or energy requirement for ≥ one third of the intervention period. Reasons for non-adherence will be registered as part of the regular contact or at follow-up visits. It is the intention to collect all data independent of deviation from the protocol.

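### Non-adherence has two conflicting definitions, and its planned odds ratios refer to a baseline at which the indicator has no meaning

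*Protocol article*

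**What the plan says.** The protocol article defines the concept in two places.

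- *Data collection for participants who discontinue or deviate from intervention protocols*: deviation means "less than 6 regular contacts and an intake of less than 80% of the calculated protein or energy requirement", lasting a third or more of the intervention. The next sentence treats this as non-adherence: "Reasons for non-adherence will be registered as part of the regular contact or at follow-up visits".
- *Non-adherence* (item 20c), intervention arm only: "an indicator of non-adherence will be defined if the following 2 criteria are met". The two criteria are fewer than 6 contacts, and intake below "80% of the calculated protein and energy requirement for at least one third of the intervention period".

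The *Non-adherence* section then plans a logistic mixed model within that arm, with time as the fixed effect and random effects for block and participant. Its output is stated as follows: "The estimated changes in non-adherence from baseline to 1 and 3 months will be reported as odds ratios".

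Two other sections bear on this. *Nutritionally augmented standard of care* sets a 12-week intervention with "phone calls from the project coordinator every 7–14th day". *Implementation* (item 16c) says that allocation is disclosed only after the baseline assessment.

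**The concern.** Two things do not fit. First, the intake condition differs between the sections, so the same participant can be non-adherent under one and adherent under the other. Second, the analysis treats as a repeated measurement something that is defined as a summary of the whole intervention. Contacts and weeks of low intake accumulate after allocation, so nothing at the baseline visit corresponds to the indicator. No other section gives it a baseline or 1-month meaning.

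At stake is whether the reported adherence result has a defined meaning. Adherence support is one of the four elements of the intervention, so readers will look for that result.

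**Working it through.** **The plan's own figure.** The protocol gives no number for adherence. Its one calculated figure is the sample size, which does not depend on this point. With a difference of 10, SD 17, two-sided 5% (assumed two-sided) and 80% power, n = 2 × (1.96 + 0.84)² × 17² / 10² = 45.3, so 46 per group. Allowing for 20% drop-out, 46 / 0.80 = 57.5, so 58, which agrees with the stated 60.

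**Step 1: the two definitions.** The contact count, the 80% level and the one-third duration agree. Only the connective between protein and energy differs. Take a participant with fewer than 6 contacts who meets the energy level but falls short on protein for a third of the period. That participant is non-adherent under the data-collection section and adherent under *Non-adherence*.

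The documents do not give the rates needed to size this. Assume that a proportion c has fewer than 6 contacts, that a proportion p is low on protein and the same p on energy, and that contacts are independent of intake.

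| c | p | Protein and energy shortfalls | *and* rule | *or* rule |
|---|---|---|---|---|
| 0.2 | 0.5 | independent | 0.2 × 0.25 = 5% (3 of 60) | 0.2 × 0.75 = 15% (9 of 60) |
| 0.1 | 0.3 | independent | 0.1 × 0.09 = 0.9% | 0.1 × 0.51 = 5.1% |
| 0.2 | 0.5 | fully coincident | 0.2 × 0.5 = 10% (6 of 60) | 10% (6 of 60) |

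The conflict can therefore change the count several-fold, or not at all if the two shortfalls always occur together.

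**Step 2: contacts that can have taken place on schedule** (elapsed days divided by the interval, rounded down).

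| Time | Every 14 days | Every 7 days | Fewer than 6? |
|---|---|---|---|
| Baseline, day 0 | 0 | 0 | everyone |
| 1 month, days 28–31 | 2 | 4 | everyone |
| 12 weeks, day 84 | 6 | 12 | only if calls are missed |

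The sixth contact falls between day 6 × 7 = 42 and day 6 × 14 = 84. The contact criterion can separate participants only in the second half of the intervention.

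**Step 3: the baseline-referenced odds ratio.** Two codings are possible.

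*Baseline coded as adherent.* This is the literal result. One third of 84 days is 28 days of low intake, and none has elapsed at baseline. With 0 of 60 events at baseline the odds are 0, and any later count k gives [k/(60 − k)] / 0, which is infinite. Adding 0.5 to each cell gives crude odds ratios of about 7.4, 14.4 and 25.2 for k = 3, 6 and 10. For k = 3 this is (3.5/57.5) / (0.5/60.5) = 7.4. These values depend on the arbitrary correction.

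*Baseline coded mechanically.* Zero contacts counts as fewer than 6, and the baseline dietary recall stands in for the intake criterion. At baseline and 1 month the indicator then equals the intake criterion alone. By 3 months it also requires missed calls. Suppose low intake stays at p throughout and a proportion c ends with fewer than 6 contacts, independently of intake. The proportion flagged falls from p to c × p although intake has not changed. With p = 0.5 and c = 0.2 it falls from 50% to 10%, and the crude odds ratio is (0.10/0.90) / (0.50/0.50) = 0.11. For p from 0.3 to 0.5 and c from 0.1 to 0.2 the range is 0.05 to 0.15. That apparent gain comes from contacts accumulating with time.

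**The case against.** The strongest reply is that little depends on this indicator. It is a within-arm description. The *Non-adherence* section itself rules out a comparison between arms, and no analysis set or primary or secondary estimate uses it. That stands, and it limits the weight of the point. Condensation for a journal is a weaker defence, because the article describes itself as the complete protocol (item 31c), and here the definition, model and reported quantity are all fixed.

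Four stronger conclusions might be inferred, and the documents do not support them.

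- *Requiring both few contacts and low intake is an error.* It is a lenient choice. *Non-adherence* is explicit that both criteria must be met. The data-collection wording could perhaps be read as two separate criteria, but most naturally says the same.
- *Reported adherence will look near-perfect whatever participants ate.* That needs a rate of completed calls that the documents do not give. At 14-day intervals a single missed call leaves fewer than 6. The protocol expects 20% drop-out and calls hospitalisation likely, and few contacts and poor intake may well occur together.
- *The odds ratios reflect only the calendar.* Under mechanical coding the baseline-to-1-month contrast reflects intake. The fault is that intake and elapsed time are mixed.
- *A null primary result could not be examined against therapy not taken.* Protein intake, energy intake and the gap to requirement are outcomes at baseline, 1 and 3 months in both arms (*Other outcomes*; Table 2), analysed by linear mixed models (*Main analysis*). Intake is also recorded regularly during the intervention (item 11c), and reasons for non-adherence are registered.

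**Conclusion.** The point holds on two counts. The two sections contradict each other on protein *or* energy against protein *and* energy. The odds ratios for change from baseline are undefined or uninterpretable as a measure of adherence. Software may still return a number under some coding, so the accurate description is that the result would have no clear meaning, not that it must come out wrong.

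The second count rests only on the protocol's own schedule: 0 contacts at baseline and 2 to 4 at 1 month, against a threshold of 6. It needs no assumed rates. The percentages in Step 1 and the odds ratios in Step 3 are illustrations under stated assumptions. They use crude odds ratios, not the mixed model's participant-specific ones.

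The reach is small. It covers the descriptive adherence result in the intervention arm and leaves the primary comparison, the other between-group analyses and the sample size as they are.

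**What to change.** 1. Reconcile the data-collection section and *Non-adherence* to one definition. Which connective and thresholds to use is the investigators' choice.
2. Replace the baseline-referenced odds ratios with the proportion non-adherent over the intervention period, one value per participant, with a 95% confidence interval. Show the contact and intake components separately, because under the joint rule anyone with 6 or more contacts counts as adherent whatever the intake.
3. If a longitudinal description is wanted, an alternative to item 2 is a per-interval indicator that starts after baseline, with the contact threshold scaled to elapsed time.
4. For change over time, refer to the planned analysis of intake minus requirement at baseline, 1 and 3 months.

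The cost is a wording change before analysis. No new data or visits are needed, and the sample size does not change.

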### Plans to give access to the full protocol, participant-level data, and statistical code {31c}

This is considered the full protocol. Thus, there are no plans for granting further access to the study protocol. Data and statistical codes may be available on request in accordance to the General Data Protection Regulations (https://intranet.regionh.dk/regi/organisation/informationssikkerhed/dataanmeldelser-og-databehandleraftaler/Sider/default.aspx).

## Oversight and monitoring

### Composition of the coordinating center and trial steering committee {5d}

Not applicable.

### Composition of the data monitoring committee, its role and reporting structure {21a}

Not applicable.

### Adverse event reporting and harms {22}

All unintended and adverse events will be registered and reported directly to the National Committee on Health Research Ethics in Denmark and to included and potential participants. Since this study is non-invasive and only includes the intake of nutritional products, we do not expect trial-related adverse events or side effects. Hospital admission and mortality are expected outcomes regardless of allocation and this outcome will be reported as part of the study.

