### Standard of care

At the Department of Pulmonary and Infectious Diseases at Copenhagen University Hospital, North Zealand, each patient is assigned with a nurse and offered an annual conversation about advance care planning. The purpose of advance care planning is to talk about disease severity, prognosis, treatment options, symptom burden, and preparation for the late stages and death. The nurses have the responsibility to maintain a personal relationship and are available by phone every working day with the possibility to get an appointment within 2 working days. A rehabilitation program combining physical training and education on all aspects of COPD is offered every second to third year, though the rehabilitation program has a very limited focus on nutrition.

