### Criteria for discontinuing or modifying allocated interventions {11b}

The risk of side effects related to intake of nutritional supplementation is considered minimal and potential side effects is expected to be mild, primarily in the form of gastrointestinal symptoms. There are no known long-term risks.

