### Strategies to improve adherence to interventions {11c}

The strategies to improve adherence to the intervention are integrated in the design in different ways. First, the adherence support and the regular contacts encourage the participant to follow the nutritional plan and remind the participant of the opportunity to ask for help and support. The regular contact also allows for adjusting the plan to improve adherence if the participant experience challenges in reaching the nutritional targets as the nutritional intake will be registered regularly during the intervention period. In addition, this conversation is also an opportunity for the participant to talk about well-being, potential side-effect or other challenges or issues or topics of interest.

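### Side effects have a stated occasion to be raised only in the intervention arm's phone calls, so mild self-reported events may be recorded more often in that arm

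*Protocol article*

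**What the plan says.** **Where side effects come up.** Protocol article, Nutritionally augmented standard of care: "In addition to standard of care, the intervention contains four elements including (1) individual nutritional plan, (2) regular contact", then adherence support and a weight diary. The regular contacts are "phone calls from the project coordinator every 7–14th day to talk about the nutritional plan, well-being, adherence, or potential side effects". On length: "The intervention has a duration of 12 weeks". The section on adherence strategies ({11c}) describes the same calls again: "this conversation is also an opportunity for the participant to talk about well-being, potential side-effect or other challenges".

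**Control arm.** Under Standard of care, participants have an assigned nurse who is "available by phone every working day with the possibility to get an appointment within 2 working days". Contact depends on the participant ringing; no scheduled call is described.

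**Both arms.** Home visits take place at baseline, 1 month and 3 months (Participant timeline {13}). The questionnaires repeated at the two follow-up visits (Baseline assessment and study questionnaires) and the rows of Table 2 include no side-effect, tolerability or gastrointestinal item.

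**Harms.** Section {22} undertakes to register all unintended and adverse events and to report them to the ethics committee and to current and potential participants. It sets no limit by arm and does not say how events are elicited. It adds that "we do not expect trial-related adverse events or side effects". Section {11b} calls the risk from supplements minimal and says that "potential side effects is expected to be mild, primarily in the form of gastrointestinal symptoms".

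**The concern.** The duty to register events is the same in both arms, but the stated opportunity to learn of them is not. Mild complaints such as gastrointestinal symptoms tend to be recorded when a conversation turns to them and missed otherwise. As written, that conversation recurs in one arm and has no stated counterpart in the other.

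The rest of the design would not correct this. The trial is open-label, one coordinator delivers the intervention and collects the data ({17a}), and the data monitoring committee and auditing sections are marked not applicable ({21a}, {23}). If registered events were later tabulated by arm, an excess in the intervention arm could reflect contact frequency, and a reader could not separate that from a true effect. The abstract says the approach should be recommended if it proves beneficial, so an interpretable account of its mild side effects would be useful.

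**Working it through.** The protocol gives no figure for harms ascertainment, so there is none to reproduce. The check counts contacts and compares the sections.

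**1. Number of calls.** Inputs: 12 weeks, one call every 7 to 14 days.
- 12 × 7 = 84 days
- 84 / 14 = 6 calls at the longest interval
- 84 / 7 = 12 calls at the shortest

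The lower figure agrees with the protocol's own adherence definition, which uses fewer than 6 regular contacts as one criterion.

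**2. Stated post-baseline contacts by arm.**

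| Contact | Intervention | Control | Side effects named? |
|---|---|---|---|
| Scheduled phone calls | 6–12 | 0 | Yes, as a topic |
| Home visits at 1 and 3 months | 2 | 2 | No |
| Nurse line, on the participant's initiative | Available | Available | No |
| Patient files (hospital contacts, deaths) | Yes | Yes | Not applicable |

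Occasions on which side effects are a stated topic: 6–12 against 0. If the visits also picked up events informally, contacts would number 8–14 (6 + 2 to 12 + 2) against 2.

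**3. Could the visit instruments stand in?** EQ-5D-5L has a pain/discomfort question, and NRS2002, repeated at 3 months, scores reduced food intake. Neither identifies a gastrointestinal symptom or records an event. Participants are asked about exacerbations and oxygen therapy at both visits in both arms (Prognostic data), so those are collected on the same schedule.

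**4. Illustration of size.** This rests on assumptions that are not in the protocol: the true symptom risk r is equal in both arms, each contact independently captures a present symptom with probability q, visits capture as well as calls do, and the symptom can be captured at any contact. With c calls:

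- Intervention recorded risk = r × [1 − (1 − q)^(c + 2)]
- Control recorded risk = r × [1 − (1 − q)^2]
- Ratio = [1 − (1 − q)^(c + 2)] / [1 − (1 − q)^2], in which r cancels

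| q | c = 6 | c = 12 |
|---|---|---|
| 0.10 | 0.570 / 0.190 = 3.00 | 0.771 / 0.190 = 4.06 |
| 0.20 | 0.832 / 0.360 = 2.31 | 0.956 / 0.360 = 2.66 |
| 0.30 | 0.942 / 0.510 = 1.85 | 0.993 / 0.510 = 1.95 |

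The ratio runs from about 1.9 to 4.1. It would be larger if visits captured less than calls, and would approach 1 if the calls rarely turned to side effects.

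**5. {11b} against {22}.** Section {11b} describes what side effects would look like (mild, mainly gastrointestinal) and rates the risk as minimal. Section {22} says none are expected. Both convey low risk, but the harms section dismisses the kind of event that {11b} names and the calls are meant to discuss.

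**The case against.** The strongest reply is that no planned comparison is at risk. Tolerability is not a primary, secondary or other outcome, and the statistical section contains no between-arm analysis of adverse events; {22} describes safety reporting. This stands. A reader might infer that the trial's tolerability comparison is invalid, or that the intervention is bound to look worse tolerated than it is. The documents support neither: there is no such comparison, and unequal capture is a possibility that the plan leaves open.

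Second, more serious events are ascertained alike. Hospital contacts and mortality come from patient files in both arms (Prognostic data). This also stands and confines the point to mild, self-reported events without hospital contact.

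Third, the calls are not described as structured enquiry. Side effects are one topic in a list joined by "or" wording, and {11c} speaks of an opportunity for the participant to raise them. Both arms also meet study staff at two visits, where events could be mentioned. This is fair and is why the size cannot be fixed. It does not remove the asymmetry, since no shared contact names side effects at all.

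Fourth, a reader might see a flat contradiction between {11b} and {22}. Section {11b} speaks of minimal risk and potential effects, so the clash is one of wording and biases nothing by itself.

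Finally, the wording of adverse-event questions may sit in data-collection forms that are not shown, and the content of the Table 1 schedule was not readable. A side-effect item there for both arms would largely answer the point. Against this, section {31c} calls the article the full protocol, and the point rests on what it states: the topic is assigned to one arm's contacts.

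**Conclusion.** The point holds in a limited form. Side effects are a stated topic on 6–12 occasions in the intervention arm and on none in the control arm, so registration under {22} may capture mild, self-reported, non-admitted events more often in the intervention arm. The direction follows from the contact schedule. The size does not: the 1.9- to 4.1-fold range depends wholly on the assumed capture probabilities and on visits capturing as well as calls.

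The primary outcome, the sample size, hospital contacts, mortality and every planned analysis are untouched. The difference between {11b} and {22} is a separate matter of wording. The change is worth making because it costs almost nothing and keeps any later by-arm account of mild events interpretable.

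**What to change.** 1. Add the same short, fixed set of gastrointestinal and general side-effect questions to the 1- and 3-month home visits in both arms.
2. State in {22} that any by-arm reporting of non-serious events uses only those visit answers.
3. List events learned during intervention calls separately, without comparison between arms. They should still be registered and reported as {22} already promises.
4. Reconcile {11b} and {22} so that they say the same thing about which side effects are anticipated.

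**Cost:** a few fields in REDCap at two visits that already take place, and a minute or two of participant time per visit. The sample size, outcomes and planned analyses do not change. For participants who have already completed follow-up, the visit answers will be missing, and the report should say so.
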